#### Randomization

Given the cluster design, we will use a minimization approach to randomization [39]. Minimization is a type of randomization where the first participant (or cluster) is randomized and subsequent selections are allocated in a way that minimizes the imbalance on specific factors between groups. This method is helpful for a design with few participants (or clusters) and has the advantage of making each condition more closely matched on key factors across the trial. To implement this, we will use a preprogrammed computer algorithm that will assign each new workplace recruited into the trial into a condition. This process will aim to balance across conditions on the following key workplace characteristics: (1) workplace type (office-based vs non–office based), (2) organization size (<200 vs >200 employees), and (3) location (Australian Capital Territory or New South Wales or Victoria vs other Australian state or territory). Once a workplace has been allocated a condition, we will discuss with their key representative what participation in the trial involves and provide them with an email or SMS text message (depending on their preferred communication with employees) with an embedded link to their assigned study recruitment website. We expect the text to read as follows:

Would you like to participate in a research study testing a new resource for supporting employee wellbeing? Learn more about your mental health and wellbeing by completing a survey and a brief online program today: <link>.

We will ask the workplaces to send invitations to all their employees themselves, with each workplace determining who from within their organization will send this invitation. This process is designed to increase ecological validity, as the goal for the program is for it to be delivered by workplaces, we expect this to be a minimal burden (ie, 1 or 2 SMS text messages or emails) on the workplace administration staff tasked with sending invitations.

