#### Participant Recruitment and Informed Consent

Participants will be recruited on the web through participating workplaces. To be eligible for the trial, potential participants must fulfill the following criteria:

Be an employee in a participating Australian workplaceBe aged ≥18 years, living in Australia, and fluent in reading and understanding EnglishHave access to a device (eg, desktop, laptop, tablet, or smartphone) and a reliable internet connection

If participants complete the abovementioned screening criteria and are not eligible, they will be informed and provided with a list of relevant help-seeking resources.

After being assigned a condition, the workplace will send a brief email or SMS text message to their employees inviting them to participate in the trial (refer to the Randomization section for an example). The email or SMS text message will contain a link to the web page containing information about the study. Then, the employees who click the link provided by their employers will be taken to the information and consent web-based page, where they will be invited to read the information that the study and provide their consent to participate in the study on the web. This process will be confidential, and their work organization will not be informed of who among their employees has consented to participate in the trial. Participants can complete the preintervention, program, and postintervention survey in a single session. Furthermore, participants can save their progress at the bottom of the screen if they wish and re-enter the survey or program at the last point they left off by reaccessing the link from their email or SMS text message. In addition, they will be sent reminders to complete the program if they have not done so within the expected time frames (Figure 1).

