#### Assessments and Blinding

Table 1 presents the trial measures and assessment time points. Assessments will occur at baseline (pretest), posttest, and 6 months after the program is completed. The trial will be triple blinded. Participants will be blinded as far as possible to the condition; they will only be informed that their workplace has been randomized to receive one of two programs: (1) an enhanced interactive mental health education program or (2) a standard written psychoeducation program. We will not provide participants with information about which program is expected to be the most effective. The statistician who will perform the analyses will be blinded to condition allocation (triple blind). Finally, assessments will also be blinded, as they rely on participants independently completing self-report measures on the web.

**Table 1 table1:** Assessment time points for the Helipad cluster randomized controlled trial of a brief workplace training program to support help-seeking for mental ill-health.

Construct	Measure	Presurvey	Postsurvey	6-month follow-up survey
Gender	What is your gender?	✓		
Age	What is your age?	✓		
Language spoken at home	What language do you usually speak at home?	✓		
Ethnicity	How would you describe your ethnicity?	✓		
Education	What is the highest level of education that you have completed?	✓		
Employment status	What is your current employment status?	✓		
Industry	What industry are you employed in?	✓		
Help-seeking intentions	GHSQ^a^	✓	✓	✓
Help-seeking attitudes	ATSPPH-SF^b^	✓	✓	✓
Help-seeking behavior: service use type and quantity	AHSQ^c^	✓		✓
Mental illness stigma	(SASS^d^-modified)	✓	✓	✓
Mental health literacy	D-Lit^e^ or A-Lit^f^ composite	✓	✓	✓
Depression symptoms	PROMIS^g^ Depression-Short Form	✓		✓
Anxiety symptoms	PROMIS Anxiety-Short Form	✓		✓
General psychological distress	DQ5^h^	✓		✓
Work and activity impairment	WPAI^i^	✓		✓
Quality of life	ReQoL-10^j^	✓		✓
Adverse events	Did you have any unexpected or negative experiences that might be related to completing this program?		✓	✓
Intervention acceptability	AIM^k^		✓	
Intervention appropriateness	IAM^l^		✓	
Intervention feasibility	FIM^m^		✓	
Debriefing	Explanation of study			✓
Interview	Interest in an interview		✓	

^a^GHSQ: General Help-Seeking Questionnaire.

^b^ATSPPH-SF: Attitudes Toward Seeking Professional Psychological Help Scale-short form.

^c^AHSQ: Actual Help-Seeking Questionnaire.

^d^SASS: Stigma and Self-Stigma Scales.

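### The trial is called triple blinded, but only the statistician is reliably blinded: participants are given telling arm labels and rate the primary outcome themselves

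*Protocol article*

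**What the plan says.** **Blinding.** The section Assessments and Blinding states "The trial will be triple blinded" and names three parts: participants (with a hedge that this is done to the extent achievable), the statistician, and the assessments. Participants are told that their workplace was randomized to one of two programs, described as "1) an enhanced interactive mental health education program or (2) a standard written psychoeducation program". The section promises not to tell them which program is expected to do better. For the third part it gives this reason: "assessments will also be blinded, as they rely on participants independently completing self-report measures on the web".

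**Recruitment order.** The Randomization section puts the workplace briefing after allocation: "Once a workplace has been allocated a condition, we will discuss with their key representative what participation in the trial involves". The representative then receives an invitation "with an embedded link to their assigned study recruitment website", and the workplace sends it to all staff, "with each workplace determining who from within their organization will send this invitation". Participant Recruitment and Informed Consent gives the same order: "After being assigned a condition, the workplace will send a brief email or SMS text message to their employees inviting them to participate".

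**The concern.** The main problem is that the blinding claim does not fit the rest of the protocol. If participants can tell which arm they are in, and the wording suggests which arm is the better one, they may answer accordingly. When the outcome is their own rating, nobody stands between that expectation and the data. The primary outcome is a stated intention on the General Help-Seeking Questionnaire, collected immediately after a program of about 20 minutes, and the effect the trial is built to detect is only 0.2 SD. A reader who takes the triple-blind label at face value would discount a bias that the design leaves open.

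The secondary problem is the order of steps. Individual consent comes after cluster allocation, so randomizing workplaces does not by itself protect the make-up of the groups within them. If the person who promotes the study in a workplace knows the arm, promotion could differ by arm.

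**Working it through.** **Step 1: test each blinding claim against the rest of the protocol.**

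| Party said to be blinded | What the protocol provides | Does the claim hold? |
|---|---|---|
| Statistician | Masked to allocation | Yes; nothing contradicts it |
| Participants | Told that the arms are an enhanced interactive or a standard written program. The Helipad Program section describes clickable diagrams, videos and quizzes; the Active Control Program section describes written modules with little interaction | Not reliably. Each label describes the visible format, so opening the program lets a participant infer the arm |
| Assessments | Called blinded because they are self-reported online | No. With self-report the participant is the assessor, so assessment is no better blinded than the participant |

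The words *enhanced* and *standard* also rank the two programs. That works against the section's own promise to keep the expected direction from participants.

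**Step 2: when the bias could act.** Under Data Collection, Overview, the baseline questionnaire comes before the program and the post-test comes straight after it. An expectation effect triggered by opening the program therefore arises after baseline. Measuring change from baseline, as the Estimand section does, cannot remove it.

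**Step 3: scale.** The protocol gives no figure for such an effect, so the sizes below are assumptions. The other inputs come from Power and Recruitment (standardized difference 0.2, ICC 0.02, 15% attrition, two-sided 0.05), using 36 workplaces of 25. Equal allocation is assumed.

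- Recruited: 36 × 25 = 900. Completers: 900 × 0.85 = 765.
- Completers per workplace: 25 × 0.85 = 21.25. Design effect: 1 + (21.25 − 1) × 0.02 = 1.405.
- Effective number per arm: (765 / 2) / 1.405 = 272.2.
- Standard error in SD units: √(2 / 272.2) = 0.0857.
- Rejection rate with no true effect and a response bias *b*: 1 − Φ(1.96 − *b*/0.0857) + Φ(−1.96 − *b*/0.0857).

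| Assumed response bias *b* (SD) | Share of the 0.2 SD target | Two-sided rejection rate with no true effect |
|---|---|---|
| 0 | 0% | 5% |
| 0.05 | 25% | about 9% |
| 0.10 | 50% | about 21% |
| 0.20 | 100% | about 65% |

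This is a normal approximation without baseline adjustment. The last row is also the power for a true 0.2 SD effect under the same approximation; how that compares with the stated 80% is a separate sample-size matter. The table applies to response bias only, not to imbalance in who enrols.

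**Step 4: recruitment order.** The stated sequence is: allocate the workplace, brief the representative, hand over the link, a sender chosen by the workplace invites staff, employees consent, baseline, program. The article does not say that the representative or sender is unaware of the arm, and it does not say that they are told it. The reference to an assigned website could mean an arm-specific page or merely a workplace-specific link.

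**The case against.** **On blinding.** The protocol hedges participant blinding, undertakes not to say which program is expected to win, uses an active time-matched control (which should narrow differences in expectation), and keeps the statistician masked. Participants in trials of visible behavioural programs often cannot be fully blinded. All of that stands, and it means that imperfect participant blinding is not in itself a fault. It does not rescue the label: the same section still claims triple blinding, and the reason it gives for blinded assessment is mistaken whatever the control.

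**On recruitment.** A reader might infer that the arm labels, or recruitment after allocation, make different people enrol in the two arms and so bias the primary result. The documents do not support that.

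- The planned invitation is one generic text that names no arm. It goes to all employees in one or two messages.
- The choice left to the workplace is who sends it, not who receives it.
- Both programs are described to participants in both arms, and nothing says the actual arm is disclosed before consent, so the labels alone cannot create arm-dependent consent.
- Employers are not told who took part.
- Intentions are measured before the program is opened, and the estimand is change from that measurement, so a baseline difference in intentions would be largely removed.

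Masking of the representative may also be specified in the full protocol, which a condensed article need not repeat. What remains is one open route: a representative or sender, briefed after allocation, who may know the arm.

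**Conclusion.** The statements that the trial is triple blinded and that assessments are blinded are not supported by the protocol's own description. Only the statistician is reliably blinded. This rests on the text alone: the labels, the visible formats, and a self-rated primary outcome taken immediately afterwards.

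The size of any resulting bias is unknown. The calculation shows only that the trial is sensitive to it: assumed response effects of 0.05 to 0.20 SD would take a nominal 5% error rate to between about 9% and 65%. It is not evidence that such an effect will occur, and the trial is not invalid.

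Differential uptake by arm is a possible risk that the order of steps leaves open. It is not a demonstrated bias, and no size can be put on it from the documents. The point is worth correcting because the changes cost little.

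**What to change.** Main changes, in Assessments and Blinding and in the participant information:

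1. Describe the arms to participants neutrally, for example *one of two online mental health and wellbeing programs*, without *enhanced* or *standard*.
2. Replace the blinding statement with: *statistician blinded; participants, and therefore self-reported outcomes, not reliably blinded*.

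Secondary changes, in Randomization and in Participant Recruitment and Informed Consent:

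3. Hold the participation discussion, and fix the sender and number of invitations, before the allocation algorithm is run for that workplace.
4. Use one common recruitment and consent page for both arms.
5. Do not disclose the arm to the representative until recruitment at that workplace closes.

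The generic invitation text and the order of baseline before program are already planned and need no change. The cost is a minor reordering of steps, a shared landing page, an ethics-approved wording change and a less favourable blinding statement. The blinding statement can be corrected even if recruitment has begun.

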#### Participant Recruitment and Informed Consent

Participants will be recruited on the web through participating workplaces. To be eligible for the trial, potential participants must fulfill the following criteria:

Be an employee in a participating Australian workplaceBe aged ≥18 years, living in Australia, and fluent in reading and understanding EnglishHave access to a device (eg, desktop, laptop, tablet, or smartphone) and a reliable internet connection

If participants complete the abovementioned screening criteria and are not eligible, they will be informed and provided with a list of relevant help-seeking resources.

After being assigned a condition, the workplace will send a brief email or SMS text message to their employees inviting them to participate in the trial (refer to the Randomization section for an example). The email or SMS text message will contain a link to the web page containing information about the study. Then, the employees who click the link provided by their employers will be taken to the information and consent web-based page, where they will be invited to read the information that the study and provide their consent to participate in the study on the web. This process will be confidential, and their work organization will not be informed of who among their employees has consented to participate in the trial. Participants can complete the preintervention, program, and postintervention survey in a single session. Furthermore, participants can save their progress at the bottom of the screen if they wish and re-enter the survey or program at the last point they left off by reaccessing the link from their email or SMS text message. In addition, they will be sent reminders to complete the program if they have not done so within the expected time frames (Figure 1).

### Outcomes

#### Estimand

In workplace employees, what is the between-group difference for the Helipad co-designed web-based program compared with the standard psychoeducation web-based program as measured by change from preintervention to immediately postintervention on help-seeking intentions on the General Help-Seeking Questionnaire (GHSQ)?

#### Primary Outcome

Help-seeking intentions (hypothesis 1) will be assessed based on increased intentions to seek help on the GHSQ completed at posttest.

#### Secondary Outcomes

Effectiveness will be compared between the Helipad co-designed interactive program condition and the standard psychoeducation web-based program condition for mental illness stigma, mental health literacy, and help-seeking attitudes (hypothesis 2), which will be assessed, respectively, based on reduced mental health stigma (Stigma and Self-Stigma Scales [40]), increased mental health literacy (Anxiety Literacy Questionnaire [A-Lit] and Depression Literacy Questionnaire [D-Lit] composite measure [41,42]), and increased help-seeking attitudes (Attitudes Toward Seeking Professional Psychological Help Scale-short form [43]) over time relative to the control condition.

In addition, we will examine the comparative effectiveness of the Helipad co-designed interactive program condition and the standard psychoeducation web-based program condition on reducing symptoms of mental ill-health and increasing quality of life and functioning (hypothesis 4). This will be determined based on reduced symptoms over time of depression (Patient-Reported Outcomes Measurement Information System [PROMIS] Depression short form scale [44]), anxiety (PROMIS Anxiety short form scale [44]), and general psychological distress (Distress Questionnaire-5 [DQ5] [45]) and increased scores on the Recovering Quality of Life (ReQoL-10) Questionnaire [46] and increased work and activity functioning (Work Productivity and Activity Impairment [WPAI] questionnaire [47]).

Finally, the relative effects of the program on increasing help-seeking behavior (hypothesis 3) will be assessed by the proportion of participants who reported seeking help from a professional source (defined as a psychologist or counselor, a psychiatrist, a family doctor or general practitioner [GP], or an EAP) in the past 6 months. We anticipate that this will be greater in the Helipad co-designed interactive program group among people with elevated symptoms of depression or anxiety relative to the control condition (standard psychoeducation only).

The primary end point for changes in mental health literacy is the posttest assessment, while for the other secondary outcomes, the 6-month follow-up assessment will be the primary end point as these outcomes take longer to elicit change.

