#### Secondary Hypotheses (Aim 2)

Hypothesis 2: Mental illness stigma will be lower and mental health literacy and help-seeking attitudes will be higher in the Helipad co-designed interactive program condition relative to the control condition (standard psychoeducation only) at posttest.Hypothesis 3: Help-seeking behavior will be greater in the Helipad co-designed interactive program condition among people with elevated symptoms of depression or anxiety relative to the control condition (standard psychoeducation only) at the 6-month follow-up.Hypothesis 4: Symptoms of mental ill-health will be lower and quality of life and functioning will be higher in the Helipad co-designed interactive program condition relative to the control condition (standard psychoeducation only) at the 6-month follow-up.

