### Data Analysis

An intention-to-treat approach to account for missing data of the mixed model repeated measures ANOVA (continuous data) or mixed effects logistic regression (binary data) will be used, adjusting for intraclass correlation to account for clustering effects within each site. Mixed models include all available data and account for within-individual variability, including those participants with missing data points, under the missing-at-random assumption [48].

Exploratory analyses will examine evidence for moderators or mediators of outcome and will be reported separately from the primary and secondary outcomes. Implementation outcomes at 6 months will be separately examined using description statistics, including *t* tests (2-tailed). The economic analysis will examine cost-effectiveness from the health sector and societal perspectives. The cost of the Helipad intervention and the active control program will be estimated using microcosting methods. Service use data will be limited in this study to health care professional visits or services accessed (internet program and helpline) specifically for mental health. The additional costs of health care resource use will be operationalized as the number of contacts with health professionals collected on the Actual Help-Seeking Questionnaire [49] (psychologist or counselor, psychiatrist, family doctor or GP, EAP, phone helpline, and internet-based treatment program). Lost productivity will also be evaluated in societal perspective costs as assessed through the WPAI questionnaire [47] and valued using the human capital approach. The ReQoL-10 Questionnaire [46] will be used to calculate utility values and quality-adjusted life years (QALYs) using the area under the curve method. Differences in costs between trial groups will be compared to the differences in QALYs through an incremental cost-effectiveness ratio (ICER) because of the inherent value-for-money connotations associated with cost-effectiveness ratios using QALYs. Additional ICERs using secondary outcomes will be calculated where the Helipad intervention is found to have an effect. Nonparametric bootstrapping will be used to determine CIs for ICERs.

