### Data Collection

#### Overview

Participants who agree to participate in the trial by clicking the link will be asked to provide an email address and complete a brief 10-minute baseline questionnaire. Following completion of the baseline questionnaire, participants will immediately be given access to the web-based program (approximately 20 minutes), which will be followed immediately by the 10-minute posttest questionnaire survey. The 10-minute follow-up survey link will be sent to participants via email 6 months after completion of their allocated condition.

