#### Help-Seeking Behavior

Help-seeking behavior will be assessed by the proportion of participants reporting seeking help from a professional help-seeking source in the past 6 months on the Actual Help-Seeking Questionnaire [49]. This questionnaire consists of 10 items measuring self-reported help-seeking behavior. Participants are provided a list of help-seeking sources (matched to the abovementioned list for the intentions scale) and asked to indicate where, if any, they have “gone to for advice or help in the past 6 months for a mental health problem*.*” Furthermore, participants can indicate if they had seen someone else not listed, that they had not spoken with anyone about their problems, or that they had not experienced any problems. The number of visits to each health professional (psychologist or counselor, psychiatrist, family doctor or GP, and EAP) or the number of times a service was accessed (internet program and helpline) will also be assessed. Items from this scale specifying the number of contacts with each health professional or service will be used for the economic analysis.

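### The Hypothesis 3 endpoint does not separate new from continuing professional help-seeking, although the baseline AHSQ would allow it

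*Protocol article*

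**What the plan says.** Hypothesis 3 reads: "Help-seeking behavior will be greater in the Helipad co-designed interactive program condition among people with elevated symptoms of depression or anxiety" than under control, at the 6-month follow-up (Secondary Hypotheses).

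Secondary Outcomes states that the behavior "will be assessed by the proportion of participants who reported seeking help from a professional source", and lists four such sources: psychologist or counselor, psychiatrist, GP and EAP. The Help-Seeking Behavior section under Measures repeats the definition: "Help-seeking behavior will be assessed by the proportion of participants reporting seeking help from a professional help-seeking source in the past 6 months". The instrument is the AHSQ, on which participants mark the sources they have "gone to for advice or help in the past 6 months for a mental health problem".

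Table 1 lists "Help-seeking behavior: service use type and quantity" at the presurvey and at 6 months. The follow-up survey link "will be sent to participants via email 6 months after completion of their allocated condition" (Data Collection, Overview). On analysis, "mixed effects logistic regression (binary data) will be used, adjusting for intraclass correlation to account for clustering effects within each site" (Data Analysis). That section also promises proportions improving, declining and unchanged on the outcome measures.

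The criteria under Participant Recruitment and Informed Consent concern employment, age, residence, English and internet access. None concerns current or recent treatment.

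**The concern.** The Introduction presents the problem as people who do not seek help, or who take years to do so. The Seeking support module explains how, where and from whom to get help. Both are about starting care. The endpoint instead measures the prevalence of any contact over 6 months.

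People who were in care at entry and stay in care add successes to both arms. If the program mainly prompts people to start, these successes carry no information about its effect, yet they enter both numerator and denominator. A null result could mean no effect, or an effect on starting care hidden by existing care. A positive result could mean more people starting, or more people staying. Hypothesis 3 is the trial's hypothesis about actual help-seeking behavior, so the distinction matters for what can be concluded.

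**Working it through.** The plan gives no event rate, effect size or power for Hypothesis 3, so there is no stated figure to reproduce. What follows illustrates the size of the dilution.

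**Inputs from the protocol article**
- Elevated symptoms expected in about 180 of 900 participants (Limitations and Risks).
- Two-sided alpha 0.05 and ICC 0.02 (Power and Recruitment, where both are set for the primary outcome).
- At least 30 workplaces (same section).

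**Assumptions, not in the documents**
- 1:1 allocation, so 90 elevated-symptom participants per arm.
- The ICC of 0.02 also applies to the binary outcome.
- Share already in care at entry, *c*: 20%, 30% or 50%.
- Share *k* of those who report contact again at 6 months: 100%, then 70–90%.
- New contact among those not in care: 15% control, 25% Helipad.
- No program effect in people already in care.

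**Step 1, dilution.** Control rate = *ck* + (1−*c*)×0.15. Helipad rate = *ck* + (1−*c*)×0.25. The difference is (1−*c*)×0.10, whatever *k* is.

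**Step 2, clustering.** 180/30 = 6 elevated-symptom participants per workplace. Design effect = 1 + (6−1)×0.02 = 1.10. Effective number per arm = 90/1.10 = 81.8.

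**Step 3, power.** Two-proportion normal approximation: Φ[(d − 1.96×SE0)/SE1], where d is the difference and SE0 and SE1 are its standard errors with pooled and separate variances. For *c* = 30%, *k* = 100%: d = 0.475 − 0.405 = 0.07, SE0 = √(2×0.44×0.56/81.8) = 0.0776, SE1 = 0.0774, power = Φ(−1.06) = 14%. The restricted analysis uses 81.8×(1−*c*) per arm and 15% versus 25%.

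Results with *k* = 100%:

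| *c* | Rates as defined | Difference | Odds ratio | Power as defined (no loss / 85% retained) | Power, not in care at entry (no loss / 85% retained) |
|---|---|---|---|---|---|
| 0% | 15.0% vs 25.0% | 10 points | 1.89 | 35.8% / 31.7% | same |
| 20% | 32.0% vs 40.0% | 8 points | 1.42 | 18.5% / 16.5% | 29.7% / 26.3% |
| 30% | 40.5% vs 47.5% | 7 points | 1.33 | 14.4% / 13.0% | 26.5% / 23.5% |
| 50% | 57.5% vs 62.5% | 5 points | 1.23 | 9.5% / 8.8% | 20.2% / 18.0% |

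The 85% columns borrow the plan's 15% pre-to-post attrition; no 6-month figure is given. They use 180×0.85/30 = 5.1 per workplace and a design effect of 1.082.

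**Step 4, incomplete continuation.** With *c* = 30–50%, *k* = 70–90% and no loss, the share of control-arm successes that is continuing care, *ck*/[*ck* + (1−*c*)×0.15], runs from 0.21/0.315 = 67% to 0.45/0.525 = 86%. Power is about 9–15% as defined and 20–27% restricted.

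**Step 5, adjusting instead of restricting.** Stratify all elevated-symptom participants by baseline contact and test the common effect: z = (n2/2×0.10)/√[n1/2×*k*(1−*k*) + n2/2×0.20×0.80], with n1 = 81.8*c* and n2 = 81.8(1−*c*). Power = Φ(z − 1.96). For the Step 4 inputs this gives about 11–22%. Adjustment recovers part of the loss.

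**The case against.** **The trial can still show initiation.** A reader might infer that the trial cannot show whether Helipad starts help-seeking. The documents do not support that: the AHSQ is taken at the presurvey and again at 6 months, so new contact among people with none at baseline can be estimated from planned data. Nor is the comparison biased under the null, because randomization balances prior care in expectation.

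**Any contact may be the intended target.** Hypothesis 3 says behavior will be greater, not newly started, and staying in or returning to care also fits the aim of better service use. This stands as a reason to keep the all-elevated comparison. It is no reason to leave initiation unreported.

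**The analysis may already cover it.** Use of baseline status could sit in an analysis plan that is not shown, and its absence from the article alone would be no finding. The endpoint, however, is fixed in the article, in two places. A repeated-measures logistic model would estimate change in any contact, which mixes starting with stopping. The improve/decline/unchanged proportions are descriptive and do not name Hypothesis 3, and unchanged would pool people always in care with people never in care.

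**The figures are assumed, and power stays low.** Both are correct. The rates are not from the documents, and zero effect in people with prior contact is assumed. The as-defined power also comes from an unadjusted test; Step 5 shows the gap narrows with adjustment. Even with nobody in care and no loss, power is about 36%, so the change does not make Hypothesis 3 well powered.

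**The recall window is minor.** One might argue that a 6-month look-back misses the first weeks after the program. The survey link goes out 6 months after completion with a reminder at 1 week, so the window nearly matches the post-program period.

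**Conclusion.** The point holds as a matter of dilution and interpretation. The endpoint as worded counts continuing care as success, and nothing in the article uses the baseline AHSQ to separate it from new contact. If the program works mainly by prompting people to start, the difference shrinks by the factor (1−*c*): from 10 points to 8, 7 or 5 under the assumed rates. The direction needs only that assumption; the size depends on a share in care that the documents do not give. If the program also keeps people in care, the shrinkage is smaller, but new and continuing contact remain mixed.

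It would go too far to call the comparison invalid or the question unanswerable. This is a secondary outcome, and low power from about 180 participants is the larger limit. The change is still worth making before the data are seen, because an initiation analysis chosen afterwards would be post hoc.

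**What to change.** 1. Keep the Hypothesis 3 comparison in all elevated-symptom participants, and adjust it for professional help-seeking at baseline (any of the four listed sources on the AHSQ, yes/no).
2. Pre-specify alongside it the proportion with new professional contact at 6 months, by arm, among elevated-symptom participants who reported none of the four sources at baseline, with the same allowance for clustering.
3. State that the first addresses any professional contact and the second addresses starting it.
4. Optionally, anchor the follow-up AHSQ question to the program date.

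Cost: a few sentences on the outcome and its analysis. Items 1 to 3 need no new data; item 4 changes one survey question. The initiation analysis has fewer people. Baseline AHSQ also records contact in the previous 6 months, not current care, so someone who had stopped before entry is left out of the initiation group even if they later start again. That is a further reason to keep the all-elevated comparison.
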